#### Secondary outcomes:

The differences between treatment groups in overall intended purchases by (i) added sugar content (g/100g); (ii) Health Star Rating (from 0.5 to 5); and (iii) percentage of Five Food Group (healthy) and discretionary (unhealthy) foods according to Australian Dietary Guidelines (13), which will be analysed using logistic or linear regression, as appropriate. Trial 2 results will be examined for the whole sample. We will then test for interaction with possible effect modifiers, including gender, age, education, and usual sugar consumption, and stratify analyses when an interaction term is significant at a p-value of <0.01. All analyses will be adjusted for key covariates.

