#### Secondary

Displaying multiple added sugar labels on food and drink items reduces the proportion of intended purchases that are high sugar products, compared no labels or display of one added sugar label.

Participant characteristics including age, gender, education, income, and usual levels of sugar consumption alter the effect added sugar labelling on intended purchasing.

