### Sample size calculations:

Sample sizes of 144 completed participant surveys per subgroup for Trials 1 and 2 are based on detection of 32% difference in intended purchasing of high versus low sugar products, with a statistical significance level of 5% and 80% power (based on Billich et al. 2018 findings, smallest difference detected between baseline purchases [64% purchased sugar sweetened beverages] compared to 28% to 47% participants across treatment groups, and approximately 10% unusable surveys due to errors)(8). Trial 1: 7 treatment groups x 144 participants per group= 1,008 participants. Trial 2: 4 treatment groups x 144 participants per group x 2 for subgroup analysis of high v. low sugar consumers= total 1152 participants.

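### Trial 2 is doubled to study high and low sugar consumers separately, but that stratified analysis depends on an interaction test at p<0.01 that was never sized

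*Protocol*

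**What the plan says.** Protocol, Sample size calculations: "Sample sizes of 144 completed participant surveys per subgroup for Trials 1 and 2" are planned, "with a statistical significance level of 5% and 80% power". The planning rates come from an earlier online trial: "smallest difference detected between baseline purchases [64% purchased sugar sweetened beverages] compared to 28% to 47% participants across treatment groups". About 10% of surveys are expected to be unusable. The Trial 2 count is four groups of 144, ending "x 2 for subgroup analysis of high v. low sugar consumers= total 1152 participants".

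Protocol, Analysis for Trials 1 and 2, Secondary outcomes: Trial 2 is analysed in the whole sample first. Interaction is then tested with "possible effect modifiers, including gender, age, education, and usual sugar consumption", and the plan will "stratify analyses when an interaction term is significant at a p-value of <0.01".

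Protocol, Hypothesis, Secondary: "Participant characteristics including age, gender, education, income, and usual levels of sugar consumption alter the effect" of the labels. The Summary and the secondary research question also name effects by participant characteristics, income among them.

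**The concern.** Only one subgroup analysis in this protocol has a sample size behind it: high v low sugar consumers. The second set of 576 participants (4 x 144) has that single stated purpose. Yet the analysis text treats this subgroup like gender, age and education, for which nothing was sized. Its strata are analysed only if an interaction passes a threshold five times stricter than the 5% used for sizing.

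An interaction contrast has a larger standard error than the comparison within one stratum, so a sample that is just adequate within strata is usually short for the interaction. Followed literally, the plan could leave undone the analysis that the extra recruitment was meant to support. This includes the case where a label works in both groups, which is itself a useful result for labelling policy.

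**Working it through.** **Inputs.** From Sample size calculations: 144 per cell, 5% level, 80% power, 64% baseline, 47% in the nearest treatment group, 28% in the farthest, 10% unusable. From Secondary outcomes: interaction threshold 0.01. Assumptions: two-sided tests (sidedness is not stated); equal strata in Trial 2, as the doubling implies; and usual sugar consumption means the same high/low split as in the sample size.

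**Reproducing 144.** For 64% v 47%, with mean rate 0.555:

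n = [1.96 x sqrt(2 x 0.555 x 0.445) + 0.842 x sqrt(0.2304 + 0.2491)]² / 0.17² = 133.

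With continuity correction n is 145. Allowing for 10% unusable gives 133/0.9 = 148, or 131/0.9 = 146 with unpooled variance. All are close to 144. The section also says the size is "based on detection of 32% difference in intended purchasing of high versus low sugar products", but that does not lead to 144: 64% v 32% needs 38-44 per group, and a 32% relative reduction (64% v 43.5%) needs 92-103. The working contrast is therefore 64% v 47%, or 17 points.

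**Within each stratum.** Usable surveys: 144 x 0.9 = 129.6, about 130. Power for 64% v 47% at 5% is 79% (83% at 144). The doubling does what it was meant to do.

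**The interaction test.** Take 64% to 47% in one stratum and 64% to 64% in the other, one outcome per participant as in the sample size.

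- Risk difference: SE = sqrt((3 x 0.2304 + 0.2491)/130) = 0.085. Power at 0.01 = Φ(0.17/0.085 − 2.576) = 28%.
- Log odds: difference 0.575 − (−0.120) = 0.695; SE = sqrt((3/0.2304 + 1/0.2491)/130) = 0.362. Power = Φ(1.92 − 2.576) = 26%.
- A joint 3-df test of arm by stratum gives 25-26%.

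**Other scenarios**, power (%) at 0.01, risk difference / log odds:

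| Scenario | 130 per cell | 144 per cell |
|---|---|---|
| 17 points in one stratum, 0 in the other | 28.2 / 25.6 | 31.8 / 29.0 |
| 17 points v 8.5 points | 5.6 / 5.2 | 6.3 / 5.8 |
| 17 v 0, three choices pooled, correlation 0.5 | 44.9 / 41.2 | 50.0 / 46.0 |
| same, correlation 0.3 | 56.4 / 52.2 | 62.0 / 57.7 |
| same, correlation 0.1 | 72.1 / 67.8 | 77.4 / 73.3 |
| 32 points v 0 | 89.5 / 85.0 | 92.7 / 89.0 |
| 36 points v 0 (64% v 28%) | 96.1 / 93.5 | 97.7 / 95.8 |

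The pooled rows use an effective size of 3n/(1 + 2ρ). The protocol gives no within-person correlation ρ, so these values are assumed.

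**Detectable difference.** On the one-outcome basis, the difference between strata that is detectable with 80% power at 0.01 is (2.576 + 0.842) x 0.085 = 0.29. That is 29 points, against a planned main effect of 17. Detecting 17 points with 80% power would need about 380-411 usable per cell, or 3,040-3,288 over eight cells. Relaxing the threshold to 0.05 gives only about 48-52% power at 130 per cell.

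**Equal effects.** If a label works equally in both strata on the modelled scale, the interaction is null. The condition is then met about 1% of the time by construction, whatever the sample size.

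**The case against.** An interaction-first rule with a strict threshold is a recognised guard against chance subgroup findings when at least four modifiers are examined. That stands: the rule is not an error in itself.

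The 26-28% is the low end of the range. Each participant makes three choices (stated under Trial 1 methods), and the primary outcome is a proportion among intended purchases, so pooling could raise power. Trial 2 also carries forward the two most effective Trial 1 labels, so effects may exceed 17 points. Both points stand, and the figure must be given as a range. The 17-point contrast remains the fair base case because it is the only one that reproduces 144.

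Three stronger readings are tempting but not supported:

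- That the plan suppresses subgroup results. The text makes stratified analysis conditional. It does not say that interaction estimates are withheld, and a fitted interaction model contains stratum-specific effects.
- That the two sections flatly contradict each other. Testing the interaction is itself a subgroup analysis, and the larger sample serves it and the whole-sample comparison. The fault is narrower: the condition was not sized, and it stands in front of the analysis that was.
- That income has been dropped. The modifier list is introduced as non-exhaustive and income is named elsewhere, so its absence there is a wording matter and adds no weight here.

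Which estimates are tabulated may be left to an analysis plan that is not shown. The protocol itself, however, fixes the threshold, the modifier and the reason for doubling.

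**Conclusion.** The concern holds as a mismatch between what was sized and what the analysis text commits to. Whether the sized subgroup analysis is carried out depends on a test with no stated power. That power is about 26-28% at 130 usable per cell (29-32% at 144) for the planning effect confined to one stratum, and about 5-6% when the second stratum has half the effect. Pooling three choices would bring the first figure to about 41-72% for assumed correlations of 0.5 to 0.1. Only one-stratum effects of 32-36 points bring it to 85-96% on the one-outcome basis. With equal effects it is about 1%.

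So the stratified analysis would often not be triggered, and almost never if a label works alike in both groups. It would be too strong to say that it will usually be lost, since that depends on a correlation and an effect size the protocol does not settle. The whole-sample primary comparison is unaffected, so this is a change that should be made rather than one that must be.

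**What to change.** In Secondary outcomes, separate the sized subgroup from the others:

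- For high v low sugar purchasers in Trial 2, always estimate and report the label effects with 95% confidence intervals in both strata, together with the interaction estimate and its confidence interval, whatever the p-value. Label this as the pre-planned subgroup analysis.
- Keep the p<0.01 rule for the modifiers that were not sized.
- As a wording note, name income in the modifier list, to match the Summary, the secondary research question and the secondary hypothesis.

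This changes wording only, with no extra recruitment or data. The downside is one more set of estimates to report. The interaction estimate and its interval beside them would keep readers from over-interpreting a difference between strata.

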## Ethical approval

A low risk ethics application will be submitted for approval from Deakin University Human Research Ethics Committee. This trial has received funding from the Deakin University Faculty of Health HAtCH 2020 grant, researchers will provide their time in-kind.

## Trial registration

The trial will be registered with Australia New Zealand Clinical Trials Registry (ANZCTR) prior to commencement.

## Data sharing

Deakin University researchers will own the data collected and will only receive the data from the recruitment company in its anonymised form. Anonymous survey data will be available to collaborators for relevant consumer behaviour research.

## Intellectual property considerations

The IP is retained by the research team listed in this application. No commercial outcomes are anticipated.

## Dissemination and publication planning

FSANZ is currently exploring options for added sugar labelling and therefore in order to ensure their policy plan is evidence-based. We will contact FSANZ (supported by [name]) and notify them about our project plan and ask for targeted feedback on policy-relevant issues. Further, once results have been finalised but prior to publication we will send them a short research brief to inform them of our results to assist with policy making. We will also send the policy brief to other parties that we believe will be useful for leveraging policy (e.g. Victorian Health Minister and NZ Ministry of Health).

Research results will be published in a peer reviewed scientific journal. Research findings dissemination will also include lay summaries and infographics to target engagement of consumers, advocacy groups and policy makers. This will include dissemination through the Obesity Policy Coalition networks (by [name]) including directly to policy makers to inform current policy consultations. As well as this, [name] (from the University of Auckland) and other research team members have close ties to policy makers through previous projects and committee memberships.

## Timeline

**Figure 1. Timeline for added sugar labelling choice experiment**

Figure 1 demonstrates the expected timeline for the project. It is expected that the project will be completed nine months, with results submitted to a scientific paper December 2020.

